## Abstract

**Background:**

Studies have confirmed that the rate of mental illness is no higher in rural Australians than that of urban Australians. However, the rate of poor mental health outcomes, and in particular suicide, is significantly raised in rural populations. This is thought to be due to lack of early diagnosis, health service access, the distance-decay effect, poor physical health determinants and access to firearms. Research conducted by the National Centre for Farmer Health between 2004 and 2009 reveals that there is a correlation between obesity and psychological distress among the farming community where suicide rates are recognised as high. Chronic stress overstimulates the regulation of the hypothalamic-pituitary-adrenal (HPA) axis that is associated with abdominal obesity. Increasing physical activity may block negative thoughts, increase social contact, positively influence brain chemistry and improve both physical and mental health. This paper describes the design of the Farming Fit study that aims to identify the effect of physical activity on psychological distress, obesity and health behaviours such as diet patterns and smoking in farm men and women.

**Methods/Design:**

For this quasi-experimental (convenience sample) control-intervention study, overweight (Body Mass Index ≥25 kg/m^2^) farm men and women will be recruited from Sustainable Farm Families™ (SFF) programs held across Victoria, Australia. Baseline demographic data, health data, depression anxiety stress scale (DASS) scores, dietary information, physical activity data, anthropometric data, blood pressure and biochemical analysis of plasma and salivary cortisol levels will be collected. The intervention group will receive an exercise program and regular phone coaching in order to increase their physical activity. Analysis will evaluate the impact of the intervention by longitudinal data (baseline and post intervention) comparison of intervention and control groups.

**Discussion:**

This study is designed to examine the effect of physical activity on psychological health and other co-morbidities such as obesity, impaired glucose tolerance, hypertension and dyslipidaemia within a high-risk cohort. The outcomes of this research will be relevant to further research and service delivery programs, in particular those tailored to rural communities.

**Trial registration:**

ACTRN12610000827033

## Background

Mental health disorders, particularly anxiety and depression, are the leading cause of health related disability in Australia [1,2]. These disorders make a large contribution to the global burden of disease, with depressive disorders being the leading cause in middle- and high-income regions such as European Union, North America, Japan and Australia [3]. By 2020, depression is projected to reach second place in the global burden of disease rankings [4,5]. Rural Australians face a high mental health burden [6] due to social isolation [7], socio-economic constraints [8,9], poor diet, increased alcohol intake, sub-optimal sleep, lack of exercise, high rates of obesity [10] and diabetes [11]. As a sub-population of rural Australia it has become evident that farmers experience inferior physical and mental health than their rural counterparts [6,12,13]. This is also due to the distance decay effect where the further people are from a service, the longer they wait to access that service [14]. The differences between rural and farmer mental health is highlighted by the increased incidence of suicide in farming communities worldwide [15-17]. A study of South Australian farmers revealed that the suicide rate on farms is 67% higher than in rural populations which, in turn, is higher than in urban South Australia [12]. Ongoing research with the Sustainable Farm Families™ (SFF) program reveals that poor health indicators are pronounced within the farming community [13,17-19]. Furthermore, our previous study [20] has revealed that, farmers had a higher rate of obesity/overweight (64.3%) when compared to national averages. Additionally, the prevalence of abdominal obesity was 8.7% higher than the Australian national average [21]. This study also revealed that 45.9% of the participants were psychologically distressed using the Kessler 10 score [22] of greater than 15, a rate significantly higher than rural Victorians (31.3%), all Victorians (34%) and national (32.7%) averages [6]. Finally, higher levels of psychological distress were positively correlated with abdominal adiposity.

Abdominal obesity has been suggested to be associated with overstimulation of the hypothalamic-pituitary-adrenal (HPA) axis [23,24] due to chronic stress [25], altering diurnal cortisol secretion. Abnormal regulation of the HPA axis and perceived stress-dependent cortisol levels are strongly related to perturbations of the endocrine axis as well as abdominal obesity with metabolic abnormalities [26].

A complex set of interrelationships occur between lifestyle, anthropometric, psychological and physical activity variables [27]. Of particular interest is the apparent relationship between physical and mental health [28,29]. Depressed people generally have lower physical activity levels than people without depression [30,31]. Lower physical activity levels also exacerbate depression resulting in a negative feedback cycle [32]. Conversely, increasing physical activity has the dual benefit of increasing physical fitness and alleviating depression and anxiety [29]. Even without the physical health benefits, increasing physical activity may block negative thoughts, distract people from worries, increase social contact and change the brain chemistry to improve mood [33]. Farming people are seldom thought of as being physically inactive, however the very nature of farming is seasonal, increasingly mechanised, with longer periods of being sedentary and greater reliance on vehicles. Further, opportunities for leisure time activity are reduced since many local sporting clubs have amalgamated or ceased to exist and access to a gymnasium or personal trainers is likely to be difficult due to distance and financial constraints.

The aim of this paper is to describe the pilot testing of the Farming Fit study which will examine the effect of physical activity on psychological health, obesity, impaired glucose tolerance, hypertension and dyslipidaemia in farm men and women.

## Methods/Design

### Intervention community

Inclusion - Farm men and women participating in SFF programs will be recruited. Participants will be recruited from rural Victoria, have been farming for more than 5 years, be aged between 18 and 75 years, speak English and live 10 kilometres or more from a regional centre with a population greater than 10, 000. All study participants will be either overweight or obese as determined by body mass index (BMI) ≥ 25 kg/m^2^.

Exclusion - Participants will be excluded from the study if they have a chronic terminal illness or are pregnant or lactating mothers. People with very high levels of psychological distress will be referred for mental health assessment by a health professional (DASS 21 Score depression > 28 or anxiety > 20 or stress > 37) [33]. Subjects unable to participate in physical activity will not be eligible to participate.

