#### Depression, Anxiety and Stress Scale - 21 items (DASS 21)

The Depression, Anxiety and Stress Scale - 21 items (DASS 21) is a set of three self-reported scales designed to measure psychological health status [52]. Each of the three DASS 21 scales contains 7 items, divided into subscales with similar content. The Depression scale consists of items that assess dysphoria, hopelessness, devaluation of life, self-deprecation, lack of interest/involvement, anhedonia, and inertia. The Anxiety scale assesses autonomic arousal, skeletal muscle effects, situational anxiety and subjective experience of anxious affect. The Stress scale is sensitive to levels of chronic non-specific arousal. It assesses difficulty relaxing, nervous arousal, and being easily upset/agitated, irritable/over-reactive and impatient. Scores for Depression, Anxiety and Stress are calculated by summing the scores for the relevant items [34,38,52].

The DASS is a quantitative measure of distress, not a categorical measure of clinical diagnoses. However for clinical purposes it can be helpful to have 'labels' to characterise degree of severity relative to the population. Thus the cut-off scores have been developed for defining mild/moderate/severe/extremely severe scores for each DASS scale (Table 2).

**Table 2 T2:** DASS 21 recommended cut-off points [34]

	Depression	Anxiety	Stress
**Normal**	0-9	0-7	**0-14**
**Mild**	10-13	8-9	**15-18**
**Moderate**	14-20	10-14	**19-25**
**Severe**	21-27	15-19	**26-33**
**Extremely Severe**	**28+**	**20+**	**37+**

**Note**: the severity labels are used to describe the full range of scores in the population, so 'mild' for example means that the person is above the population mean but probably still below the typical severity of someone seeking help[34].

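### The DASS 21 referral rule leaves out the first score of the trial's own top severity band, and Table 2 leaves stress scores 34 to 36 in no band

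*Protocol article*

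**What the plan says.** The protocol article sets the referral rule in Methods/Design, Intervention community, in the paragraph on exclusion. It states that "People with very high levels of psychological distress will be referred for mental health assessment by a health professional" and defines that group as "DASS 21 Score depression > 28 or anxiety > 20 or stress > 37". The inequality is strict on all three scales, and the citation given is [33].

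The section on the DASS 21 says that "the cut-off scores have been developed for defining mild/moderate/severe/extremely severe scores for each DASS scale" and gives them in Table 2, citing [34]. The two highest bands in that table are:

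| Scale | Severe | Extremely Severe |
|---|---|---|
| Depression | 21-27 | 28+ |
| Anxiety | 15-19 | 20+ |
| Stress | 26-33 | 37+ |

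The note under the table says that "the severity labels are used to describe the full range of scores in the population". On scoring, the article says only that "Scores for Depression, Anxiety and Stress are calculated by summing the scores for the relevant items"; it mentions no multiplier.

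**The concern.** The three referral limits equal the three lower limits of the Extremely Severe band. Only the sign differs: the table includes the limit and the rule excludes it. Staff who follow the rule as printed would not refer someone on a score that the trial's own table places in its highest category.

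The stress column has a second defect. Its bands are meant to label every score, but three whole numbers between Severe and Extremely Severe have no label. One of the limits beside the gap must be wrong, and one of them, 37, is also the stress referral limit.

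What is at stake is participant safety and clinical labelling. This is the only DASS referral rule the article states, and its Background stresses raised suicide rates among farmers and a 45.9% rate of psychological distress in an earlier study of farmers.

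**Working it through.** **Inputs.** Referral limits come from the exclusion paragraph (depression > 28, anxiety > 20, stress > 37). Band limits come from Table 2.

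**Step 1: are the bands contiguous?** For whole-number scores, the step from one band's upper limit to the next band's lower limit should be 1.

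| Scale | Boundaries (upper limit, next lower limit) | Steps |
|---|---|---|
| Depression | 9, 10; 13, 14; 20, 21; 27, 28 | 1, 1, 1, 1 |
| Anxiety | 7, 8; 9, 10; 14, 15; 19, 20 | 1, 1, 1, 1 |
| Stress | 14, 15; 18, 19; 25, 26; 33, 37 | 1, 1, 1, 4 |

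Eleven of the 12 boundaries step by 1. The last stress boundary steps by 37 − 33 = 4, which leaves 4 − 1 = 3 scores (34, 35, 36) in no band.

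**Step 2: does the rule cover the top band?** With a strict inequality on whole numbers, the lowest referred score is the limit plus 1.

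| Scale | Top band starts at | Lowest score referred | Top-band score not referred |
|---|---|---|---|
| Depression | 28 | 29 | 28 |
| Anxiety | 20 | 21 | 20 |
| Stress | 37 | 38 | 37 |

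The rule is one point late on every scale.

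**Step 3: does this depend on which scores can occur?** The article does not say that subscale sums are doubled. Assuming they were, only even scores would occur. Depression 28 and anxiety 20 would still be missed. Stress 37 could not occur, so the sign would make no difference on that scale. Stress 34 and 36 would still have no band.

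**Step 4: what would a corrected stress limit add?** The article does not show which limit is wrong, so the range below assumes that the unlabelled scores belong to one or both of the neighbouring bands. Each count is relative to the printed > 37.

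| Top stress band starts at | Corrected rule | Scores added (whole numbers) | Scores added (even only, assumed) |
|---|---|---|---|
| 37 (Severe extended to 36) | ≥ 37 | 37: one | none |
| 36 | ≥ 36 | 36, 37: two | 36: one |
| 35 | ≥ 35 | 35, 36, 37: three | 36: one |
| 34 (Severe stays 26-33) | ≥ 34 | 34, 35, 36, 37: four | 34, 36: two |

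**Step 5: could the strict sign be a lost ≥?** The same section prints the inclusive sign for the weight criterion, "determined by body mass index (BMI) ≥ 25 kg/m^2", so there is no indication that the symbol was dropped when the text was extracted.

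**The case against.** The strongest reply is that the link between rule and band is inferred. The exclusion paragraph does not use the label Extremely Severe and does not point to Table 2; it cites [33] where the table cites [34]. A trigger that starts one point into the top band could be deliberate. The link is indeed an inference, but a strong one: all three numbers coincide, and no reason is given for starting one point late on every scale. The Background cites [33] for the effect of exercise on mood, whereas the article elsewhere cites [34] for the DASS, so [33] here is more likely a citation slip than a separate source of thresholds.

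The reply can add that the practical effect is small. The three criteria are joined by *or*, so a person at depression 28 is still referred if anxiety or stress exceeds its limit. Nothing forbids referral below the trigger, and trained health professionals carry out the physical assessments, which include a general medical and behavioural one. This is right, and it limits the claim to referral on that score alone.

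The gap in the stress labels has no shown effect on any analysis: the article treats the DASS as a quantitative measure, and the statistical section states no analysis that uses the bands. The number 37 also appears in two places while 33 appears once, so 37 may well be the correct one. This stands too. The gap by itself does not show that the stress referral limit is wrong, only that it needs checking.

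Finally, the rule sits among the exclusions, and the article does not say whether referred people remain in the study. If they are excluded, moving the limit changes eligibility for people at the boundary scores. That point is fair and qualifies any statement that the correction leaves the trial data untouched.

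**Conclusion.** The concern holds, as a minor one. As printed, the rule does not refer on depression 28 or anxiety 20, both Extremely Severe in Table 2. This is so whether scores take all whole numbers or only even ones. Stress 37 is missed as well if it can occur. The gap in the stress bands at 34 to 36 is plain on the face of the table and conflicts with the note under it.

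The first part assumes that the referral group was meant to be the Extremely Severe band, which rests on the match of all three numbers. Whether the stress referral limit is also too high cannot be settled from the article; depending on the true limit, the correction adds between one and four whole-number stress scores, or none to two if only even scores occur. How many participants would be affected cannot be derived. The sample size calculation, which rests on cortisol and body weight, and the method for analysing DASS as a continuous score are unaffected. Who enters that analysis could change slightly, but only if referral means exclusion.

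**What to change.** - In the exclusion paragraph, word the rule as depression ≥ 28, anxiety ≥ 20 and stress ≥ the lower limit of the top stress band.
- Check the stress limits against the source cited for Table 2 ([34]) and correct the rule's citation if [33] is a slip. If the top band starts at 37, extend Severe to 26-36 and set the referral limit at ≥ 37. If it starts lower, change the table entry and lower the stress referral limit to match.
- In the same edit, state whether a referred person stays in the study, since that decides whether the corrected limit touches eligibility.

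The cost is a one-line change to the rule, a correction to one table column and possibly a few more referrals. Cluster assignment and the sample size calculation do not change.

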### Preparation for evaluation

The project design is based on the analysis of data collected by the ongoing SFF program [13]. A logic model of the "farming fit cycle" describes the complex relationship of psychological distress and obesity among farm men and women - see Figure 1[20]. The study protocol detailed here has been specifically designed to measure how increasing physical activity effects pre-intervention variables (anthropometry, biochemistry, nutritional behavior, physical activity behavior and DASS) [34]. Three data collection time points will be utilised to track participant progress (baseline, 12 weeks and 24 weeks).

**Figure 1 F1:**
[figure not shown]
**Farming fit study model illustrating the relationship between psychological distress, physical activity and obesity **[20].

### Study design

This is a 6-month quasi-experimental control intervention study. Intervention and control group participants whom fulfil the abovementioned criteria will be selected from SFF programs. SFF program groups (clusters) will be randomly assigned to control and intervention groups with participants from each cluster being assigned to the same group to minimise the contamination effect.

The proposed intervention includes:

**1**. An individualised exercise coaching program for the intervention group designed by an exercise physiologist and undertaken over the entire 6-month period.

**2**. An exercise physiologist/research assistant to provide consultation on individualized exercise programs and coach over the 6-month period.

**3**. Regular monitoring of exercise activity and exercise goals by phone, email and/or mobile text message.

Participant's anthropometric and basic physical assessments and psychological assessments (DASS 21 scores) will be measured. Venous blood samples following a 10-hour fast will be taken for biochemical analysis of lipids, glucose and cortisol levels. Salivary cortisol measurements will be taken. Diet and physical activity data will be obtained using self reported questionnaires based on previously developed instruments [35,36]. Data collection will be repeated following completion of the 6-month intervention.

Diet and physical activity questionnaires and salivary cortisol samples are to be repeated following an interim 3-month period of the proposed study as outlined in Table 1. Participants from the intervention group will receive a personalised exercise program and regular phone coaching in order to promote increased physical activity.

**Table 1 T1:** Data collection and timeline for both intervention and control groups

Variable	Base line	3 month	6 month
Body weight (kg)	✓	**X**	✓
Height (cm)	✓	**X**	✓
Waist circumference (cm)	✓	**X**	✓
Hip circumference (cm)	✓	**X**	✓
Body fat (%)	✓	**X**	✓
Blood pressure (mmHg)	✓	**X**	✓
Pulse rate (bpm)	✓	**X**	✓
Fasting blood glucose (mmol/L)	✓	**X**	✓
Fasting blood cholesterol (mmol/L)	✓	**X**	✓
Fasting triglycerides (mmol/L)	✓	**X**	✓
HDL (mmol/L)	✓	**X**	✓
LDL (mmol/L)	✓	**X**	✓
Fasting blood cortisol (nmol/L)	✓	**X**	✓
Salivary cortisol*(nmol/L)	✓	✓	✓
DASS score	✓	✓	✓
Dietary questionnaire	✓	✓	✓
Physical activity questionnaire	✓	✓	✓

* Salivary cortisol will be measured by taking 4 readings/day (9 am, 12 pm, 4 pm and 8 pm)

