#### Data entry, handling and statistical analysis

Data will be tabulated and analysed using PASW^® ^statistics 18 software. Variables will be reported as means with 95% confidence intervals. Repeated measures ANOVA, paired sample t-tests, multiple linear regression, and binary logistic regression will be used to test for intervention effects after adjusting for relevant co-variables (e.g. sex, age) and baseline scores. Since physical activity scores are likely to reflect a non-normal distribution, comparisons between the sexes at baseline and over time will be performed using the Kruskal-Wallis test. Linear regression analysis will be used to assess the association between body fat percentage, body mass index and cortisol levels. Correlation coefficients between body composition, physical activity, and metabolic variables will be calculated using Pearson's and Spearman's correlation as appropriate. P values will be considered statistically significant at P < 0.05.

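### Whole SFF groups are randomised without linking the calendar timing of the two arms, so start season can be unbalanced by chance if groups start at different times of year

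*Protocol article*

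**What the plan says.** - **Allocation.** Study design states that "SFF program groups (clusters) will be randomly assigned to control and intervention groups", and that all participants from one cluster go to the same arm. It names no blocking, stratification or common start period.
- **Source of the groups.** The abstract says that participants "will be recruited from Sustainable Farm Families™ (SFF) programs held across Victoria, Australia". No section gives the number of groups, their size or their start dates.
- **Seasonality.** Background explains why farmers may be inactive by saying that "the very nature of farming is seasonal, increasingly mechanised, with longer periods of being sedentary and greater reliance on vehicles".
- **Interval.** Study design says "This is a 6-month quasi-experimental control intervention study". Preparation for evaluation puts the visits at baseline, 12 and 24 weeks. In Table 1, body weight and fasting blood cortisol, the two variables named in Sample size, are measured only at baseline and 6 months. Both arms follow the same visit schedule.
- **Analysis.** The statistical section tests intervention effects "after adjusting for relevant co-variables (e.g. sex, age) and baseline scores". Impact and outcome evaluation adds that the two groups will be compared with each other.

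**The concern.** Members of one SFF group probably share a locality and a start date, so season acts at the level of the unit that is randomised. The number of units available to balance it is the number of groups, not the 70 participants.

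A group first measured in a busy season and last measured in a quiet one may have a different expected 6-month change from a group measured in the reverse order. Adjusting for baseline score does not capture this, because the baseline value does not say which way the season is about to turn. If one arm holds more groups of one kind, the difference between arms in 6-month change contains part of the seasonal difference. Physical activity is the obvious candidate, given what Background says about farming. For weight, diet, stress and cortisol, a seasonal movement is plausible, but the article does not assert it.

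**Working it through.** The plan gives no figure on this point, so there is nothing to reproduce. The check asks how often random assignment would leave season unbalanced, and by how much that would shift the estimate.

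**Inputs from the article:** assignment by whole group (Study design); a minimum of 64 participants, so 32 per arm, and a sought effect of 0.5 SD in body weight (Sample size).

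**Assumptions, not in the article:** K groups, half assigned to each arm; half the groups starting in each of two opposite seasons; a difference D between the two start seasons in expected 6-month change, on the same SD scale as the sought effect.

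**Step 1. Chance of imbalance.** There are C(K, K/2) equally likely allocations, and 2 of them confound arm with season completely.

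| Groups | Complete confounding | Any imbalance |
|---|---|---|
| 4 | 2/6 = 33% | 2/6 = 33% |
| 6 | 2/20 = 10% | 20/20 = 100% |
| 8 | 2/70 = 3% | 34/70 = 49% |
| 10 | 2/252 = 0.8% | not used |

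The 100% with 6 groups arises only because three groups per season cannot be split evenly. In 18 of those 20 allocations the imbalance is the mild 2:1 against 1:2.

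**Step 2. Shift in the estimate.** Shift = D × (difference between arms in the proportion of groups starting in one season). That difference is 1 for complete confounding, 1/2 for 3:1 against 1:3, and 1/3 for 2:1 against 1:2. With D assumed to be 0.2 to 0.6 SD:

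- complete confounding: 0.2 to 0.6 SD
- 3:1 split: 0.1 to 0.3 SD
- 2:1 split: 0.07 to 0.2 SD

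**Step 3. Type I error averaged over allocations.** This takes 32 per arm, no season term, no other cluster effect and a standard error of √(2/32) = 0.25 SD. With 4 groups and D = 0.5 SD, a completely confounded allocation shifts the test by 0.5/0.25 = 2 standard errors and rejects with probability 0.516. The average is (1/3)(0.516) + (2/3)(0.05) = 0.205.

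| Groups | D = 0.25 SD | D = 0.5 SD |
|---|---|---|
| 4 | 9% | 21% |
| 6 | 7% | 14% |
| 8 | 7% | 12% |
| 10 | 6% | 10% |

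If all groups start in the same period, or if season is balanced, the difference in Step 2 is zero and the error rate returns to 5%.

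**The case against.** The strongest reply is that the article never says that groups start in different seasons. A reader might infer that a follow-up spanning opposite seasons is enough to mix season with intervention. It is not: controls on the same calendar undergo the same seasonal change, and the between-arm contrast removes it. This stands, and it makes the point conditional on staggered starts.

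A reader might also infer a systematic bias. The documents do not support that. Groups are assigned at random, so the expected imbalance in season is zero. Chance imbalance is part of the between-group variance, and an analysis that respects the clusters would carry it in its standard error. This stands too, so the error rates in Step 3 overlap with the general effect of ignoring clustering and should not be added to it. What remains is that only one allocation will be analysed, and a poor one is avoidable in advance.

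Nor does the statistical section exclude season: its list of covariates is given by example and is open. Blocking and visit dates may be set out in a fuller protocol.

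Finally, the sizes rest on assumptions. The number of groups need not be small, since the eligibility limits may leave few participants per group. With 10 groups complete confounding is rare. A spring-to-autumn interval may also show little seasonal change. All of this is fair, and it limits the claim to a conditional one.

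**Conclusion.** The point holds as a conditional weakness of the design. The article identifies farming as seasonal, randomises whole groups, and measures its sizing outcomes only at two visits about half a year apart, yet does not link the timing of the arms. If starts are staggered and groups are few, start season can be unbalanced by chance. Complete confounding then occurs in 33%, 10% or 3% of allocations with 4, 6 or 8 groups, given equal arms and an even split over two opposite seasons. With a seasonal difference of 0.2 to 0.6 SD, such an allocation would shift the estimate by an amount comparable with the 0.5 SD sought for body weight. The number of groups, the split and the seasonal difference are all assumed.

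The documents do not show that the arms differ in season or that the estimator is biased over repeated randomisation. If all groups start together, the problem does not arise.

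**What to change.** In Study design, state that the SFF groups of both arms run in the same calendar period. If they cannot, randomise groups in blocks defined by start window, with both arms represented in each block and the baseline, 3- and 6-month visits aligned within the block. Where a block has an odd number of groups, some imbalance remains, but complete confounding is ruled out.

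In the statistical section, add start season to the adjustment covariates when starts are staggered. Adjustment alone is not enough, because it cannot separate season from arm in a completely confounded allocation. The blocking therefore has to be fixed before groups are assigned.

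The change needs no extra participants and costs nothing if all groups start together. Otherwise a group may have to wait for its block, and the season term uses one degree of freedom. In a group-level comparison of two arms (K − 2 residual degrees of freedom), that is a fall from 2 to 1 with 4 groups, 4 to 3 with 6, and 6 to 5 with 8. With so few groups, a compulsory pair term or matching on farm type as well is not recommended.

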### Sample size

To evaluate the intervention, sample size was determined at the power of 80% (β = 0.2) with α set at 0.05 for an effect size of a standard deviation change of fasting serum cortisol and/or a 0.5 standard deviation reduction of body weight by the end of the intervention. This required the sample size to be a minimum of 64 participants across the control and intervention groups [37]. By considering the probable retention rate (≥95%) for a 6-month intervention the target recruitment number was fixed at a minimum of 35 participants in both the control and intervention groups, requiring recruitment of a total of 70 farming participants meeting the above criteria.

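### SFF groups are randomised as whole clusters, but neither the sample size nor any named test of the intervention allows for clustering

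*Protocol article*

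**What the plan says.** Allocation is by group. The Study design section says that "SFF program groups (clusters) will be randomly assigned to control and intervention groups with participants from each cluster being assigned to the same group". The reason it gives is to limit contamination between arms. The protocol article itself calls these groups clusters. The abstract introduces the design with "For this quasi-experimental (convenience sample) control-intervention study".

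The Sample size section says that "sample size was determined at the power of 80% (β = 0.2) with α set at 0.05". One target is "an effect size of a standard deviation change of fasting serum cortisol". The other, offered as an addition or alternative, is a fall of 0.5 SD in body weight. The section arrives at a minimum of 64 across both arms. After a retention rate of at least 95%, it sets 35 per arm, "requiring recruitment of a total of 70 farming participants meeting the above criteria". Power, alpha, effect size and retention are the only inputs. There is no ICC, group size, number of groups or design effect.

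The section on data entry, handling and statistical analysis says that "Repeated measures ANOVA, paired sample t-tests, multiple linear regression, and binary logistic regression will be used to test for intervention effects", adjusted for baseline scores and covariates, of which sex and age are given as examples. Significance is judged at P < 0.05. SFF group appears in none of these methods. No mixed model with a group effect, GEE, cluster-robust variance or cluster-level analysis is named anywhere in the article.

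**The concern.** When whole groups are allocated, the comparison between arms carries variation between groups as well as between people. An individual-level test counts each participant as independent information. If members of a group resemble one another on the outcome, the standard error is too small, the confidence interval too narrow and the P value too low. Repeated measures ANOVA and paired t-tests do not help: they deal with correlation within one person over time, not between members of the same group.

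The same correlation reduces the information in 64 people. With few groups per arm, a valid test also has few degrees of freedom, so the number of groups matters as well as the number of participants. The number of groups is not stated, so a reader cannot check the claimed power.

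At stake are every between-arm P value and interval. The Discussion intends the results to inform further research and service delivery.

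**Working it through.** **Inputs from the article:** alpha 0.05 (taken as two-sided; sidedness is not stated), power 80%, effects of 1 SD (cortisol) and 0.5 SD (body weight), 64 evaluable in two equal arms (32 each), retention 95%.

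**Inputs assumed, because the article gives neither:** m = 5 to 15 eligible participants per SFF group; ICC = 0.02 to 0.10.

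**Step 1. The plan's own figure.** For two independent means, n per arm = 2(1.960 + 0.842)²/d².
- d = 0.5: 15.70/0.25 = 62.8, so 63 per arm (64 by the t distribution), 126 to 128 in total.
- d = 1: 15.7, so 16 per arm (17 by the t distribution), 32 to 34 in total.

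Neither target gives 64 in total; 64 is the per-arm number for 0.5 SD. With 32 per arm and full independence, power is 50% for 0.5 SD and 98% for 1 SD. That mismatch is separate from clustering, but it is the starting point for what follows. The retention step is sound: 64/0.95 = 67.4, and 70 covers it.

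**Step 2. Effect of clustering.** DE = 1 + (m − 1) × ICC. Effective n per arm = 32/DE. The real type I error of a nominal 5% test that ignores groups is 2[1 − Φ(1.96/√DE)]. Power is from the two-sample t-test at the effective n.

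| m | ICC | DE | Effective n per arm | Type I error | Power, 0.5 SD | Power, 1 SD |
|---|---|---|---|---|---|---|
| any | 0 | 1.00 | 32 | 5.0% | 50% | 98% |
| 5 | 0.02 | 1.08 | 29.6 | 5.9% | 47% | 97% |
| 10 | 0.05 | 1.45 | 22.1 | 10.4% | 37% | 90% |
| 15 | 0.10 | 2.40 | 13.3 | 20.6% | 24% | 70% |

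For example, in the third row DE = 1 + 9 × 0.05 = 1.45, 1.96/√1.45 = 1.628, and the two-sided tail area is 0.104.

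**Step 3. Few groups.** The power columns above still use individual-level degrees of freedom. A t-test on k group means per arm has 2k − 2 degrees of freedom and noncentrality d/√(2·DE/(mk)). For 3 groups of 11 per arm at ICC 0.05, DE = 1.5, the noncentrality for 1 SD is 1/√(3/33) = 3.32, and there are 4 degrees of freedom. Results at ICC 0.05:

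| Groups per arm × size | Power, 1 SD | Power, 0.5 SD |
|---|---|---|
| 2 × 16 | 39% | 15% |
| 3 × 11 | 70% | 25% |
| 4 × 8 | 82% | 31% |
| 6 × 5 | 89% | 36% |

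Simulation of the 3 × 11 case with no true effect gives about 11% false positives for the test that ignores groups, and about 5% for the test on group means.

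**The case against.** Several points on the other side have force.

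- **The power loss is not all due to clustering.** A reader might set 24% to 47% for body weight beside the stated 80% and blame clustering for the whole gap. The figures do not support that. The drop from 80% to 50% comes from 64 not being a two-arm total for 0.5 SD. Clustering accounts only for the further fall from 50%.
- **The cortisol target has slack.** At 34 needed against 64 planned, it can absorb a design effect of about 64/34 = 1.88 before power drops below 80%, provided there are enough groups. It would be wrong to say that power is overstated for every target in every scenario. Still, with 3 groups per arm at ICC 0.05 it is about 70%, and the number of groups is unknown.
- **Baseline adjustment could raise power.** If the SDs are raw SDs, a baseline correlation of about 0.70 (√(1 − 32/63)) would bring 32 per arm to 80% for 0.5 SD under independence. The sample size section does not invoke this, and it does not remove dependence between group members.
- **The size is assumed.** With small groups and a low ICC, type I error is barely above 5%. The intervention is individualised and delivered remotely, with no group exercise sessions described. The article does not say that group members share a facilitator, household or farm industry, so no particular cause of correlation can be asserted.
- **A separate analysis plan may add a cluster term.** It may, and this makes the analysis half less firm than the sample size half. But the article names its tests of the intervention, and the open covariate list cannot rescue them: SFF group as an ordinary fixed covariate is nested in arm and would absorb the intervention effect. Nor can a later plan add a clustering allowance to a recruitment target already fixed at 70.
- **The quasi-experimental label.** A reader might infer that it conceals a cluster-randomised design. It does not: the Study design section states random assignment of clusters openly, and the abstract ties the label to convenience sampling. The wording is loose, no more.
- **Pilot status.** The Background speaks of pilot testing, but the article claims 80% power and tests at P < 0.05, so the tests need to hold their level.

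**Conclusion.** The point holds. The plan allocates clusters and then sizes and tests the study as if individuals had been allocated, and nothing elsewhere in the article repairs this. The direction (P values too small) depends on a positive ICC, which is the usual expectation for people recruited through the same group. The size depends on the assumed ranges. Over them, a nominal 5% test has a real level from just under 6% to about 21%, so the consequence runs from minor to serious and cannot be pinned down until group numbers and sizes are stated. The power conclusion must be kept separate by target: cortisol starts with a margin that clustering may or may not use up, while body weight is underpowered before clustering is considered and more so after. The type I error problem stands whatever is decided about the 64. It should be fixed before any between-arm result is reported.

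**What to change.** **Analysis section.** Test intervention effects with a linear mixed model that has a random intercept for SFF group, the baseline value, sex and age as covariates, and Satterthwaite or Kenward-Roger degrees of freedom. A t-test on baseline-adjusted SFF-group means is an acceptable alternative. For binary outcomes, replace plain logistic regression with the corresponding mixed-model or cluster-level analysis.

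**Sample size section.** State the number of SFF groups per arm and the assumed ICC, and restate power separately for the cortisol and body weight targets with clustering allowed for.

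**Design description.** Call the study cluster-randomised wherever the design is described (abstract, Study design, Impact and outcome evaluation), alongside the convenience-sample wording.

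**Cost.** The analysis change is a few lines of text and one model term. Confidence intervals widen and the stated power falls. No extra participants are needed for valid inference, but the change only discloses the power shortfall. Restoring 80% would mean recruiting more groups, and the sponsor should say whether that is intended.
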